### Patient safety

Adverse events (AE) and serious adverse events (SAE) may occur during the acupuncture and moxibustion treatment or neuroimaging scanning. For example, possible adverse events due to acupuncture include subcutaneous hemorrhage, severe pain, and fainting. Possible adverse events due to moxibustion include blisters, redness, itching, and burns. All adverse events will be treated immediately and recorded in the case report form (CRFs) in detail throughout the trial. SAEs will be reported to the Research Ethics Committee within 24 h. Furthermore, all events will be evaluated for their relevance to the intervention and severity.

### Data management and monitoring

Data will be collected by a dedicated researcher, and the quality of the data will be supervised by two independent researchers. The communication between researchers and participants will be strengthened to improve adherence and to promote participant retention. The clinical data will be recorded accurately and timely in printed CRFs. All the neuroimaging data will be stored in dedicated hard drives after every scanning is completed. The Ethics Committee of the First Teaching Hospital of Chengdu University of TCM will be supervising this trial and will make the final decision to terminate the trial. The process will be independent from the investigators and the sponsor. The data safety monitoring board (DSMB) will be established to ensure patient safety and data confidentiality. The DSMB will conduct ongoing safety monitoring and meet every 3 months.

### Data analysis

A detailed statistical analysis plan (SAP) was developed before the initiation of the statistical analysis. The data analysis will be completed by statisticians who are independent from the research team. The SAP includes clinical data analysis and neuroimaging data processing and analysis.

### Clinical data analysis

The Kolmogorov-Smirnov test will be used to test the normal distribution of continuous variables. Continuous variables on normal distribution will be presented by mean ± standard deviation, while continuous variables of skewed distribution were expressed as medians and interquartile ranges (IQRs). Analyses will be performed on an intention-to-treat basis. Multiple imputations will be used to handle the missing data. Paired samples *t*-test will be used to compare the clinical outcomes between baseline and end of treatment in each group. Since there are three groups (acupuncture group, moxibustion group, and waiting-list group) with two time points (pre-treatment and post-treatment), the repeated measures analysis of variance (ANOVA) will be employed to analyze the clinical data. In the 2 × 3 group factorial design, the dependent variables were the clinical data collected from pre-treatment and post-treatment, and data in the three different groups will serve as the independent variable. ANOVA and chi-square test will be used to compare group differences at baseline. ANOVA with Šidák corrections will be used to compare the differences between the groups. Clinical data on skewed distribution will be compared using a non-parametric test. A two-sided test is applied for available data, and a *P* value of less than 0.05 is considered statistically significant. Missing data will be replaced by the data from the latest assessment.

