#### Measurements for the quality of life

The 36-item Short Form Health Survey (SF-36) will be used to evaluate the quality of life [32]. The scale contains 8 dimensions including physical functioning, role limitations due to physical health problems, role limitations due to emotional problems, social functioning, bodily pain, vitality, mental health, and general health.

The VAS, CMSS, and PCS will be measured at baseline and every menstrual cycle throughout the treatment. The SAS, SDS, and SF-36 will be measured at baseline and at the end of the treatment.

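### The pre/post repeated-measures ANOVA compares change scores and gives cycles 1 and 2 no role; adjusting for baseline as a covariate would be more precise with the data already collected

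*Protocol article*

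**What the plan says.** The schedule and the model do not describe the same data. Under *Measurements for the quality of life*, the protocol article states: "The VAS, CMSS, and PCS will be measured at baseline and every menstrual cycle throughout the treatment". Table 1 agrees, with VAS, CMSS and PCS marked at months 0, 1, 2 and 3. SAS, SDS and SF-36 are taken only at baseline and at the end of treatment.

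Under *Clinical data analysis*, the model is chosen for three groups "with two time points (pre-treatment and post-treatment), the repeated measures analysis of variance (ANOVA) will be employed to analyze the clinical data", and "the dependent variables were the clinical data collected from pre-treatment and post-treatment". No baseline covariate is named.

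Two further analyses stand beside it. Paired t-tests "will be used to compare the clinical outcomes between baseline and end of treatment in each group". Between groups, "ANOVA with Šidák corrections will be used to compare the differences between the groups". Tests are two-sided, and a P "value of less than 0.05 is considered statistically significant".

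The first aim, at the end of *Background*, is to compare acupuncture with moxibustion, which is a between-group question.

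**The concern.** There are three linked points.

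- **Model and schedule.** The two-point premise is right for SAS, SDS and SF-36. It is wrong for VAS, CMSS and PCS, the three scales that the abstract names for clinical efficacy. Their cycle 1 and cycle 2 values have no place in the named model. They could enter only through the sentence that replaces a missing value by the latest assessment.
- **Use of baseline.** The model takes baseline into account by subtraction. A randomised comparison has a more precise alternative in the same data, namely baseline as a covariate. The arms have 24 patients each, a number taken from an imaging rule of thumb and not from a clinical power calculation, so avoidable imprecision matters.
- **Within-group tests.** A paired t-test measures change over time in one arm. It does not separate treatment from other causes of change, and it cannot show that one treatment is better than another. Patients are unblinded and must have had a VAS of at least 4 cm in the last period, so some improvement in every arm is plausible.

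**Working it through.** The article states no clinical effect size, SD, correlation or power, so there is no clinical figure to reproduce.

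**Inputs from the article.** 24 per arm (*Sample size*); two-sided 0.05 with Šidák correction between groups (*Clinical data analysis*).

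**Assumptions.** Three pairwise contrasts under Šidák; equal SD (set to 1) before and after treatment; correlation r between baseline and final score of 0.3, 0.5 or 0.7; true difference at cycle 3 of 0.7 SD.

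**Step 1: what the group-by-time term tests.** With two time points, its F statistic equals the F of a one-way ANOVA on change scores. A numerical check gave 1.7046 for both.

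**Step 2: variance.** A change score has variance 1 + 1 − 2r = 2(1−r). The final score adjusted for baseline has residual variance 1 − r². The ratio of change score to ANCOVA is 2(1−r)/[(1−r)(1+r)] = 2/(1+r). This is above 1 for every r below 1, and it does not depend on the effect size.

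**Step 3: level per contrast.** 1 − 0.95^(1/3) = 0.01695.

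**Step 4: power.** The standardised effect is 0.7/√variance, the noncentrality is that effect × √(24/2), and power comes from the noncentral t with 46 degrees of freedom. The small cost of estimating the covariate slope is ignored.

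| r | Variance, change | Variance, ANCOVA | Patients needed, ratio | Effect, change | Effect, ANCOVA | Power, change | Power, ANCOVA |
|---|---|---|---|---|---|---|---|
| 0.3 | 1.40 | 0.91 | 1.54 | 0.592 | 0.734 | 34% | 53% |
| 0.5 | 1.00 | 0.75 | 1.33 | 0.700 | 0.808 | 48% | 63% |
| 0.7 | 0.60 | 0.51 | 1.18 | 0.904 | 0.980 | 74% | 82% |

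The gap narrows as the assumed effect grows. At 1.0 SD the same calculation gives 67, 83 and 97% for change against 87, 93 and 99% for ANCOVA.

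**Step 5: the paired tests.** If nothing changes in any arm, three independent tests at 0.05 give at least one false positive with probability 1 − 0.95³ = 14.3% per outcome. Now suppose that every arm improves by the same 0.5 SD and there is no treatment effect. With n = 24, each paired test is then significant with probability p = 0.51, 0.65 or 0.86 at r = 0.3, 0.5 or 0.7. Two given arms disagree on significance with probability 2p(1−p), about 0.50, 0.45 or 0.24. A finding of significant change in one arm and not in the other would therefore often arise without any difference between the treatments.

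**Step 6: what cycles 1 and 2 add.** If the target is the cycle 3 difference and the data are complete, a longitudinal model with unstructured covariance gains essentially nothing over ANCOVA at cycle 3. The gain in the table comes from the covariate. The intermediate cycles help mainly when cycle 3 values are missing.

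**The case against.** The strongest reply is that this concerns efficiency alone. Differencing removes baseline, and randomisation makes the comparison unbiased. Looking at the end of treatment is a legitimate choice, and it matches the other three scales and the two MRI scans. The size of the loss rests on an effect and correlations that the article does not give. All of this stands, and it limits how serious the point is. It does not remove the point: the loss of precision has the same direction at every r below 1, and avoiding it needs no new data.

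Some stronger readings are tempting, and the document does not support them.

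- *Baseline is ignored.* It is not; it is subtracted.
- *Leaving out cycles 1 and 2 wastes much power.* That would follow for an average over the three cycles with a constant effect. If the effect instead builds up linearly to 0.7 SD at cycle 3, power for the three-cycle mean is about 49, 52 and 66% (with equal correlation r between all occasions). That is below ANCOVA at cycle 3 throughout, and below the planned test at r = 0.7.
- *The Šidák comparisons average pre and post values and so halve the effect.* The text says only that the "corrections will be used to compare the differences between the groups". The section on methodological quality control speaks of comparing symptom improvement, which points to change.
- *The paired tests are the evidence of efficacy.* They are not declared decisive, and they stand beside between-group comparisons. The separate SAP that the article mentions may rank the tests.
- *The non-parametric alternative loses the baseline adjustment.* The article does not say which test is meant or on what data, and a rank test on change scores would keep the subtraction.

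**Conclusion.** The point holds as one of precision and of fit between model and schedule. The article describes the clinical data as having two time points, while its three efficacy scales have four occasions. Its group-by-time test needs 2/(1+r) times the patients that a baseline-adjusted comparison needs. That ratio assumes equal variances before and after treatment, and it is 1.54, 1.33 or 1.18 at r = 0.3, 0.5 or 0.7. At 0.7 SD the difference in power is about 19, 14 or 8 percentage points; because effect and correlation are assumed, this contradicts no figure in the article. The paired t-tests cannot answer the first aim.

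A reader might infer that the planned comparison is biased or invalid. It is not. This should be fixed before the analysis, but the trial's conclusions do not fail without it.

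**What to change.** Change the analysis wording before the data are analysed:

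1. For VAS, CMSS and PCS, fit one longitudinal model per scale to cycles 1 to 3, with baseline score, group, cycle and group-by-cycle as fixed effects and an unstructured covariance. Name the baseline-adjusted between-group difference at cycle 3 as the decisive contrast.
2. For SAS, SDS and SF-36, use ANCOVA on the end-of-treatment score with baseline as covariate.
3. Apply the Šidák correction to those pairwise contrasts, and say so.
4. Report within-group changes with confidence intervals as description only, without tests.

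The cost is a few sentences and slightly more analysis work. No extra visits, questionnaires or patients are needed: every value used is already in Table 1. Additional scores from the 3-month baseline period are not proposed. Table 1 schedules none before month 0, and by the dates under *Trial status* recruitment was due to end before the article appeared.

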### Sample size

According to the statistical requirements of neuroimaging studies, 12–15 individuals in each group is the reasonable sample size for stable cerebral responses [22, 23]. Considering a drop-out rate of 20% and possible excessive head motion during scanning, a sample size of 24 in each group is required, and a total of 72 PDM patients will be recruited.

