### Randomization and blinding

Randomization will be implemented using computer-generated randomization digital table which is created by Excel’s rand function. Seventy-two eligible PDM patients will be randomly assigned to the acupuncture group, moxibustion group, and waiting list group (1:1:1 ratio). Random information will be put into an opaque, sealed envelope and saved by those who will not participate in the study. Due to the particularity operation of acupuncture and moxibustion, it is difficult to blind operators and patients. However, outcome assessors and statisticians were blinded to the procedure and the result of randomization, group allocation, and intervention to reduce the risk of bias.

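### A normality check on the trial's own data chooses between ANOVA and an unnamed non-parametric test, and the Šidák correction is stated only for the ANOVA route

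*Protocol article*

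**What the plan says.** All the relevant text is in the Clinical data analysis section of the protocol article.

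- **Normality check:** "The Kolmogorov-Smirnov test will be used to test the normal distribution of continuous variables". The result is tied explicitly to the descriptive format (mean and SD, or median and IQR).
- **Main analyses:** a paired t-test of baseline against end of treatment within each group, and a repeated-measures ANOVA over three groups and two time points.
- **Between-group comparisons:** "ANOVA with Šidák corrections will be used to compare the differences between the groups".
- **Skewed data:** "Clinical data on skewed distribution will be compared using a non-parametric test".
- **Level:** "A two-sided test is applied for available data", and a P "value of less than 0.05 is considered statistically significant".

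The opening of the Data analysis section says that a detailed SAP covers the clinical analysis. That document is not available here.

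**The concern.** The section gives no other definition of skewed, so the natural reading is that the Kolmogorov-Smirnov result sends each scale down one of two routes. The first route is fully described: a pre-post model with corrected comparisons among three groups. The second is described only as non-parametric.

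The first stated aim is to compare acupuncture with moxibustion, and this section governs that comparison on every clinical scale. If the route is chosen after the data are seen, the multiplicity control and the contrast tested (post-treatment score, change, or within-group difference) could differ from scale to scale. For a borderline scale they could turn on which version of the normality test the software runs.

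**Working it through.** **Inputs from the protocol article.** Three groups, hence three pairwise comparisons per scale. Two-sided 0.05. "a sample size of 24 in each group is required, and a total of 72 PDM patients will be recruited". The article gives no distribution, effect size or pre-post correlation for any clinical scale, so those below are assumptions.

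**1. The stated correction.** Šidák level per pair = 1 − (1 − 0.05)^(1/3) = 0.01695. Check: 1 − (1 − 0.01695)^3 = 0.050. The ANOVA route is therefore set at 5% per scale.

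**2. The skewed route, by what the unnamed test might be.** Three uncorrected tests at 0.05 would give 1 − 0.95^3 = 0.143 if independent. Pairs share groups, so the true figure is lower. Simulation with no group difference, 24 per arm, 6000 runs; ranges run over normal, gamma (skewness 1) and log-normal (sigma 0.6) scores:

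| Test used on the skewed route | Family-wise error within a scale |
|---|---|
| Three rank-sum tests at 0.05 | 0.115 to 0.119 |
| Three rank-sum tests at 0.01695 | 0.039 to 0.040 |
| Kruskal-Wallis, alone or before pairwise tests | 0.046 to 0.047 |

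A separate log-normal simulation gave 0.12, 0.041 and 0.050.

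**3. The whole two-route procedure.** Only data that fail the normality check reach the skewed route. With a Lilliefors-type Kolmogorov-Smirnov test on all 72 values, Šidák t-tests if passed and uncorrected rank-sum tests if failed:

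| Data | Share sent to skewed route | Error, skewed route uncorrected | Error, Šidák on both routes |
|---|---|---|---|
| Normal | 3% | 0.043 | 0.041 |
| Gamma, skewness 1 | 48% | 0.078 | 0.041 |
| Log-normal, sigma 0.6 | 92% | 0.111 | 0.039 |

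**4. The version of the check matters.** The plain Kolmogorov-Smirnov test with estimated parameters sends about 0%, 4% and 43% of the same data sets to the skewed route. The procedure's error is roughly share × rank-sum error + (1 − share) × Šidák t-test error. For log-normal data under the Lilliefors form this gives 0.924 × 0.117 + 0.076 × 0.038 = 0.111, matching the simulation. Under the plain form:

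- log-normal: 0.432 × 0.117 + 0.568 × 0.038 = 0.072
- gamma: 0.039 × 0.115 + 0.961 × 0.0415 = 0.044

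**5. The form of the outcome matters too.** Assumed 0.8 SD difference between two arms, 24 per arm, tested at 0.01695:

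| Pre-post correlation (assumed) | Rank test on post score | Rank test on change | Rank ANCOVA on baseline |
|---|---|---|---|
| 0.3 | 0.58 | 0.41 | 0.63 |
| 0.5 | 0.57 | 0.56 | 0.70 |
| 0.7 | 0.57 | 0.82 | 0.86 |

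Post score beats change at low correlation and loses at high correlation. Baseline adjustment is the most powerful at all three values. With two time points, the group-by-time test of the planned repeated-measures ANOVA is a comparison of change.

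**The case against.** The strongest reply is that the article condenses a SAP. The name of the non-parametric test, the variable it is run on and its post hoc adjustment are details commonly left to that document. This stands. A reader might infer that skewed scales will be tested without correction and with the pre-post contrast dropped, but the article says neither. Its paired t-test and repeated-measures ANOVA sentences carry no normality condition, and a non-parametric test could be a signed-rank test, a rank test on change, or Kruskal-Wallis with adjusted follow-up tests.

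It also stands that a doubled false-positive rate is not an established consequence. It needs three rank-sum tests with neither an omnibus test nor a correction, and even then the procedure as a whole has less inflation than the skewed route alone. Nor can one say that ignoring baseline always costs power against this plan: at an assumed correlation of 0.3, post scores do better than change.

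A further reply is that the rule is written in advance and the statisticians are blinded to allocation, so the test is not chosen on the treatment result. That is fair, and it limits the scope for deliberate selection. It does not answer the main point. Choosing the analysis by a check on observed data is what the article itself prescribes, not a detail it omits. A SAP that repeated the rule would still leave each scale's analysis open until the data are in.

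**Conclusion.** The point holds in limited form. The article lets the observed distribution choose the analysis of each clinical scale and states multiplicity control for one route only. Contrasts and error rates may therefore differ between scales.

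The size is conditional. With three uncorrected rank-sum tests, family-wise error within a scale is about 0.12 on the skewed route. For the whole procedure under moderate to strong skew it is about 0.08 to 0.11 with a Lilliefors-type check, and about 0.04 to 0.07 with the plain test. With Kruskal-Wallis, alone or as a first step, it stays near 0.05 and there is no inflation to report. These figures rest on assumed distributions with 24 analysed per arm. The power figures also rest on an assumed 0.8 SD effect and correlations of 0.3 to 0.7.

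The change is still worth making, because it removes the ambiguity at almost no cost and gains power over the assumed range.

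**What to change.** In the Clinical data analysis section, or in the SAP before any outcome data are analysed:

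1. State that the normality check decides only whether descriptive tables show mean ± SD or median (IQR). It does not choose the test.
2. For every clinical scale, name one between-group analysis: ANCOVA of the end-of-treatment score on the baseline score, with the Šidák correction over the three pairs whatever the distribution.
3. Name a rank ANCOVA at the same Šidák level as the pre-stated sensitivity analysis for skewness.

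The cost is one or two sentences and no extra data. Some P values for skewed scales become slightly larger than uncorrected ones would be. The power gain depends on the pre-post correlation, which the article does not give.

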**Methods:**

In this randomized controlled neuroimaging trial, 72 patients with PDM will be randomly assigned to three groups: acupuncture treatment group, moxibustion treatment group, and waiting list group. The acupuncture treatment group and moxibustion treatment group will receive acupuncture or moxibustion, respectively, for a total of 3 sessions over 3 consecutive menstrual cycles, and the waiting list group will not take acupuncture or moxibustion during these 3 menstrual cycles. The COX Menstrual Symptom Scale (CMSS), visual analog scale (VAS), and Pain Catastrophizing Scale (PCS) will be used to evaluate the clinical efficacy. The Self-rating Depression Scale (SDS), Self-rating Anxiety Scale (SAS), and 36-Item Short Form Health Survey (SF-36) will be used to assess the mental state and quality of life at baseline and at the end of treatment. Functional magnetic resonance imaging (fMRI) will be performed for detecting the cerebral activity changes at baseline and at the end of the treatment. The clinical data and imaging data will be analyzed among the groups. Correlation analysis will be conducted to investigate the relationship between brain functional changes and symptom improvement.

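### No primary clinical outcome is named: efficacy can be claimed at P<0.05 on CMSS, VAS or PCS, with a false-positive chance of about 11–14% instead of 5%

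*Protocol article*

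**What the plan says.** The abstract states: "The COX Menstrual Symptom Scale (CMSS), visual analog scale (VAS), and Pain Catastrophizing Scale (PCS) will be used to evaluate the clinical efficacy". For the other instruments it says that the SDS, SAS and "36-Item Short Form Health Survey (SF-36) will be used to assess the mental state and quality of life". No section calls any of these primary or secondary. The first aim, at the end of the Background, is to compare acupuncture with moxibustion, and it names no scale.

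The Clinical data analysis section refers to clinical outcomes or clinical data without distinguishing among them. It fixes the design as "Since there are three groups (acupuncture group, moxibustion group, and waiting-list group) with two time points (pre-treatment and post-treatment"), to be analysed by repeated-measures ANOVA. On error control it says "ANOVA with Šidák corrections will be used to compare the differences between the groups", then "A two-sided test is applied for available data", with a P "value of less than 0.05 is considered statistically significant". It mentions no adjustment across scales.

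The Sample size section takes 24 per group from an imaging convention and ties it to no clinical scale.

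**The concern.** With three unranked efficacy scales and one flat threshold, the stated rule is met as soon as any one of them crosses 0.05. The trial could then be reported as showing efficacy on a scale picked after the results are known, at an error rate above the 5% that a reader would assume. The Šidák correction does not prevent this, because it works within a scale, across the group contrasts.

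**Working it through.** **Does the sample size reveal a primary outcome?** The plan's own figure is 24 per group, from 12–15 evaluable, a 20% drop-out and an unquantified loss to head motion. 12/(1−0.20) = 15 and 15/(1−0.20) = 18.75, so 19. Since 24 × 0.80 = 19.2, reaching 24 needs a further loss of 1 − 15/19.2 = 22% to 1 − 12/19.2 = 37.5%, which is not stated. The figure can be neither confirmed nor called wrong. It contains no effect size, SD or power for any clinical scale, so it does not point to a hidden primary outcome.

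**Inputs for the error rate.** Alpha is 0.05 two-sided (Clinical data analysis). There are three efficacy scales and three further scales (abstract). One between-group test per scale is counted, at the end of treatment. Correlations of 0.5 and 0.7 between scales are assumptions.

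**Formulas.** For k independent scales, the chance of at least one false positive is 1 − 0.95^k:
- k = 3: 1 − 0.857 = 14.3%
- k = 6: 1 − 0.735 = 26.5%

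For equally correlated normal test statistics with correlation r, it is 1 − ∫ φ(u)[Φ((1.96 − u√r)/√(1−r)) − Φ((−1.96 − u√r)/√(1−r))]^k du. As a check, 20,000 three-group trials with 24 per group were simulated for each setting. One version used the overall F test on each scale, the other Šidák pairwise tests within each scale.

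| Scales | Correlation | Formula | Simulated, F per scale | Simulated, Šidák pairs per scale |
|---|---|---|---|---|
| 3 | 0 | 14.3% | 14.5% | 12.8% |
| 3 | 0.5 | 12.5% | 12.6% | 11.2% |
| 3 | 0.7 | 10.9% | 11.3% | 10.1% |
| 6 | 0 | 26.5% | 26.5% | 23.8% |
| 6 | 0.5 | 20.7% | 21.6% | 19.3% |
| 6 | 0.7 | 16.4% | 17.2% | 15.5% |

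The last column shows that Šidák between groups leaves the error across scales at twice the nominal level or more. None of these figures counts the paired t-tests planned within each group.

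**Šidák between groups.** Three groups give three pairs (inferred; the article does not list the contrasts), so each pair is tested at 1 − 0.95^(1/3) = 0.01695. In 100,000 simulated trials with 24 per group and no true difference, the family-wise error was 4.4%, so the correction is valid.

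**Closed alternative.** With three groups, if two pairwise nulls are true the third is too. The true nulls therefore number three, one or none. A gate that holds 5% under the global null, followed by pairs at 0.05, keeps family-wise error at 5% in every case. The gate can be the smallest pairwise P below 0.01695, or a significant global test. In simulation neither version exceeded 5.0%. Power per true contrast, with one arm an assumed 0.8 SD from the other two:

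| n per group | Šidák | Closed, smallest P | Closed, global F |
|---|---|---|---|
| 24 | 63% | 71% | 73% |
| 19 | 50% | 58% | 61% |

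**The case against.** The strongest reply is that the article refers to a separate statistical analysis plan, not shown, which may hold rules for the secondary scales. That stands for the adjustment of secondary scales. It stands less well for the choice of primary outcome, which a protocol normally fixes. This article also goes as far as stating the alpha and a multiplicity method, and on that text all scales are equal.

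Three stronger readings are tempting, and the documents do not support them.
- A reader might infer that efficacy can be claimed on any of six scales. The abstract ties efficacy to CMSS, VAS and PCS and gives SDS, SAS and SF-36 to mental state and quality of life. The six-scale figure applies only if all clinical outcomes are counted as equals, as the analysis section treats them.
- A reader might count the eight SF-36 dimensions separately, making 13 scores and 49% if independent. The article lists the dimensions but does not say that each is tested.
- A reader might conclude that Šidák spends alpha in the wrong place. Correction between groups and correction across scales are separate matters. Dropping Šidák would release nothing for the scales, and keeping it does not cause the gap.

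It is also fair to say that the power gain rests on assumed effects and is modest in one respect: in the 0.8 SD case with 24 per group, the chance of finding any true or false difference moves only from 78% to 81%. Nor is VAS the only sensible primary: CMSS is listed first in the abstract, and analgesics are allowed at high VAS scores, which may affect the VAS itself.

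**Conclusion.** The point holds for the three efficacy scales. As published, the plan names no primary clinical outcome and controls no error across scales, so a claim on any one of CMSS, VAS or PCS carries a false-positive chance of 14% if they are independent and about 11–12.5% at correlations of 0.7–0.5. Counting all six scales equally it is 16–26%. These figures assume one 5% test per scale and equal correlation between scales.

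This should be settled before analysis, because it decides what the trial may conclude. The Šidák correction is not an error. Replacing it with a closed test is only an optional gain in power, under effect sizes that the article does not supply.

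**What to change.** **Needed.** By dated amendment before unblinded analysis, name one primary clinical scale and its time point. VAS at the third treatment cycle is one candidate, since VAS sets eligibility and is recorded every cycle; the diary's analgesic records should then be considered in interpreting it. CMSS is another. Make the remaining scales secondary with Holm adjustment, or label them exploratory. If the unseen analysis plan already names a primary outcome, state it in the article.

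**Cost.** The change is to the text, but it is not free. The first patient was enrolled on 1 March 2021 and recruitment was due to finish before 30 June 2022, so the amendment must disclose that the choice was made after enrolment began. The other scales lose the ability to support an efficacy claim alone.

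**Optional.** For the primary scale, replace single-step Šidák with one of the closed tests above. If the global gate is used, define it as the group-by-time test or the baseline-adjusted end-of-treatment difference. The group main effect of the planned 2 × 3 ANOVA averages the two time points, so a treatment difference of δ that is absent at baseline shrinks to (0 + δ)/2 = δ/2. The smallest-P version never misses a pair that Šidák would find; the F-gated version occasionally can. Neither gives matching simultaneous confidence intervals.
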